## Abstract

**Background:**

Infants born <30 weeks’ gestation are at increased risk of long term neurodevelopmental problems compared with term born peers. The predictive value of neurobehavioural examinations at term equivalent age in very preterm infants has been reported for subsequent impairment. Yet there is little knowledge surrounding earlier neurobehavioural development in preterm infants prior to term equivalent age, and how it relates to perinatal factors, cerebral structure, and later developmental outcomes. In addition, maternal psychological wellbeing has been associated with child development. Given the high rate of psychological distress reported by parents of preterm children, it is vital we understand maternal and paternal wellbeing in the early weeks and months after preterm birth and how this influences the parent–child relationship and children’s outcomes. Therefore this study aims to examine how 1) early neurobehaviour and 2) parental mental health relate to developmental outcomes for infants born preterm compared with infants born at term.

**Methods/Design:**

This prospective cohort study will describe the neurobehaviour of 150 infants born at <30 weeks’ gestational age from birth to term equivalent age, and explore how early neurobehavioural deficits relate to brain growth or injury determined by magnetic resonance imaging, perinatal factors, parental mental health and later developmental outcomes measured using standardised assessment tools at term, one and two years’ corrected age. A control group of 150 healthy term-born infants will also be recruited for comparison of outcomes. To examine the effects of parental mental health on developmental outcomes, both parents of preterm and term-born infants will complete standardised questionnaires related to symptoms of anxiety, depression and post-traumatic stress at regular intervals from the first week of their child’s birth until their child’s second birthday. The parent–child relationship will be assessed at one and two years’ corrected age.

**Discussion:**

Detailing the trajectory of infant neurobehaviour and parental psychological distress following very preterm birth is important not only to identify infants most at risk, further understand the parental experience and highlight potential times for intervention for the infant and/or parent, but also to gain insight into the effect this has on parent–child interaction and child development.

## Background

Improving medical technologies are assisting younger and smaller preterm infants to survive. Very preterm infants (defined as born at <32 weeks’ gestation) are at risk of long-term neurodevelopmental problems including cognitive, motor and behavioural impairments [1]. The most immature infants are at the greatest risk for later neurodevelopmental deficits, yet it is these infants whose early neonatal neurobehavioural development we understand the least. In particular, there is a lack of knowledge surrounding early neurobehavioural trajectories between birth and term equivalent age. Nor do we currently understand the relationships that altered neurobehavioural trajectories may have with other important factors such as perinatal complications, cerebral structure, and later developmental outcomes [2].

Whilst many decades ago newborn infants were considered passive, research has shown that the brain, not just the spinal cord, is involved in the infant’s responses, and, more importantly, the infant’s brain is active from birth [3]. Neonatal neurobehavioural examinations have been developed that assess the integrity of an infant’s central nervous system [4] and can be used as a tool to identify infants at risk of developmental disabilities [2]. These examinations include traditional neurological assessment items such as reflexes, posture and tone along with behavioural assessment items such as the infant’s ability to regulate their own level of arousal and states, to habituate, to attend and orient [5]. Neurobehavioural development of preterm infants differs from that of term born infants at term equivalent age [6,7] and has been shown to be related to environmental and biological factors [8]. Importantly, these differences in neurobehavioural developmental at term in preterm children compared with term born children are associated with later motor, cognitive and behavioural difficulties [5,9] and contribute to neurodevelopmental impairments in school-age children born preterm. A recent review of neonatal neurobehavioural assessments for preterm infants assessed the validity of the available tools for assessing neurobehaviour from birth to term equivalent age and concluded that there are several tools that are predictive of development at age one and two years’ corrected age (CA) when used at term equivalent age and beyond [2,10,11]. However, there is a lack of evidence for the discriminative, evaluative and predictive validity of these tools when administered prior to term, limiting their use in clinical practice and research with preterm infants while in the Neonatal Intensive Care Unit (NICU). It is essential that health professionals can assess neurobehaviour from birth to (i) determine whether a very preterm infant is developing normally or abnormally, (ii) assess the effects of interventions and exposure to perinatal variables, and (iii) predict whether the infant may have long term developmental problems, so that appropriate interventions can be commenced immediately. Preliminary evidence suggests that neurobehaviour in the ex-utero environment matures rapidly during the neonatal period in association with cerebral maturation in the very preterm infant. In a small study of preterm infants born between 28 and 32 weeks’ gestational age (GA), structural and biochemical cerebral maturation (from 32 to 40 weeks’ GA), as determined by Magnetic Resonance Imaging (MRI), was reported to accompany neurobehaviour maturation [12]. At term equivalent age, preterm infants had less developed grey and white matter than full term infants and less mature neurobehaviour. It is well known that the period between 20–40 weeks’ GA is one characterised by rapid and vulnerable neurodevelopment [13]. Brain structural abnormalities in neonates are readily detected with MRI, and studies have reported that infants born <30 weeks’ GA have grey and white matter abnormalities [14], white matter microstructural alterations [15], deficits in brain connectivity [16], and volume reductions in other brain regions and structures [17-19]. Despite this, there has been a paucity of information to date relating the evolution of neurobehavioral alterations prior to term with cerebral alterations, especially for the most immature infants. Brain MRI during the neonatal period in preterm infants may help us to understand how early neurobehavioural development in this period relates to brain injury or structural alterations at term-equivalent age.

Furthermore, it has been suggested that modification to care practices and environmental stimulation can alter the developmental pathways of preterm infants [20]. In a small randomised controlled trial of preterm infants born between 28 and 32 weeks’ GA, Als et al. reported that modification to care practices and the environment in the NICU enhanced brain function and structure compared with standard care [20,21]. Given the potential to devise therapeutic interventions to aid development for preterm children, it is essential that we map the trajectory of neurobehavioural development prior to term age, and in particular prior to 32 weeks’ GA, in the ex-utero environment.

Alterations in neurobehaviour may manifest in a preterm infant being more irritable, taking longer to settle into a routine, and being less playful, compared with children born at term [22,23]. These child characteristics have the potential to influence the parent–child relationship, which provides the most proximal and immediate environmental context for development [24]. Characteristics of the parent also influence the parent–child relationship, with one of the most salient being parental wellbeing. Parents of infants born preterm can experience a range of responses following the birth, including symptoms of depression [25-29], anxiety [30-32], and post-traumatic stress [33]. Symptoms of depression, anxiety and stress in the post-natal period have been associated with changes in maternal behaviour such as increased maternal negativity, impairment in ability to recognise infant cues [34], reduced maternal sensitivity, increased maternal intrusiveness, and less optimal parenting behaviour [32]. Importantly, parental mental health problems have been shown to be associated with children’s later social emotional difficulties and mental health problems [35,36]. Therefore it is important that we understand more about parental wellbeing after the birth of a very preterm baby, how it changes over time, and how it relates to the parent–child relationship and child outcomes. The majority of previous studies have looked at parental wellbeing close to discharge from hospital, and usually only at one or a small number of time points, meaning that little is known about how parents adjust and cope in the first weeks after the preterm birth. In addition, the majority of studies examining parental wellbeing have focused on mothers, meaning that much less is known about paternal wellbeing following the birth of a very preterm child and how this influences children’s outcomes. Having detailed information on parental wellbeing for both parents and how it changes during the neonatal and early childhood period is important not only so appropriate supports can be implemented whilst the family is still within the hospital system and then potentially on an ongoing basis if needed, but also to know how parental psychological distress over the early years interacts with parenting beliefs and behaviours, and affects children’s outcomes. We plan to explore predictors for identifying parents who are likely to have continued psychological distress at one and two years following the birth, by examining parent characteristics such as beliefs about parenting competence, personality, previous history of mental health problems, significant life events and social risk during the neonatal period.

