### Aims

The main aims of this study are to:

1. Describe the evolution of early neurobehavioural development in infants <30 weeks from birth to two years’ CA compared with children born at term, and to explore how neurobehaviour is influenced by perinatal variables.

2. Explore the relationship between early neurobehavioural development and neonatal brain abnormalities (development and injury) at term using multi-modal MRI in infants <30 weeks at birth.

3. Investigate the predictive validity of neurobehavioural assessments during the early neonatal period for developmental outcomes at one and two years’ CA in infants <30 weeks at birth.

4. Examine symptoms of depression, anxiety, and post-traumatic stress in mothers and fathers of infants <30 weeks at birth and to describe changes in parental psychological wellbeing over the first two years of the child’s life compared with children born at term.

5. Examine parental psychological wellbeing, and parent and family factors during the neonatal period as predictors of development at one and two years’ CA in children born <30 weeks, and whether these relationships are similar in children born at term.

In addition, secondary aims of this study are to:

1. Explore whether neurobehavioural examinations in the preterm period relate to concurrent physiological status (i.e. heart rate and oxygen saturations) in infants <30 weeks at birth.

2. Describe the parenting beliefs and practices of parents of infants <30 weeks at birth across the first two years of the child’s life.

3. Examine whether parental psychological wellbeing from birth to one year CA is associated with the parent–child relationship and child development when the child is one and two years’ CA in infants <30 weeks at birth.

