3. The validity of early neurobehavioural assessments from birth to term-equivalent age for predicting development at one and two years’ CA in very preterm children will be investigated using separate linear (continuous outcomes) and logistic (binary impairment outcomes) regression models for each neurobehavioural assessment time point according to chronological and gestational age and each outcome. Estimates of the regression coefficients and the R^2^ values (representing the proportion of variability in the outcome explained by the model) from these models will be compared with estimates from the same models using neurobehaviour at term equivalent age as the predictor to obtain an idea of the predictive ability of these early measurements compared with the measurements at term as used currently. Data from term-born controls will be used to provide a local-reference population for calculation of mild, moderate and severe developmental impairment (mild = more than 1 SD below the mean, moderate = more than 2 SD below the mean, severe = more than 3 SD below the mean on the Cognitive Composite Scale on the Bayley-III).

4. To examine symptoms of depression, anxiety, and post-traumatic stress in mothers and fathers of very preterm children at birth during the first two years of the child’s life compared with term-born controls, we will present means and 95% CI for each parental assessment at each time point. For each time point, the observation closest to the specified time for the completed week within +/− 3.5 days for weekly assessment and +/− 7 days for fortnightly assessments will be selected for each individual.

5. To examine the relationships between parental psychological wellbeing, parent and family factors, and very preterm children’s neurobehavioural development at birth, and later two year-old cognitive, motor and social-emotional developmental outcomes, we will fit separate linear regression models for each of the two year outcomes. Initially each parent and child factor will be explored using separate univariable models for each outcome before combining important factors into a single model for each outcome to assess independent predictors.

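### Aim 3 judges prediction of binary impairment by coefficients and an R² that has no single definition for logistic models and does not show discrimination; the AUC would serve better

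*Protocol article*

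**What the plan says.** In the Background, the article states that "there is a lack of evidence for the discriminative, evaluative and predictive validity of these tools when administered prior to term". It lists three things health professionals need from early assessment, the third being "iii) predict whether the infant may have long term developmental problems, so that appropriate interventions can be commenced immediately".

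Under Aims, main aim 3 is to "Investigate the predictive validity of neurobehavioural assessments during the early neonatal period for developmental outcomes" at one and two years' corrected age.

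Under Data collection & analysis, item 3 specifies "separate linear (continuous outcomes) and logistic (binary impairment outcomes) regression models for each neurobehavioural assessment time point" and for each outcome. It then names what will be compared: "Estimates of the regression coefficients and the R^2^ values (representing the proportion of variability in the outcome explained by the model) from these models". The comparator is the same model with the term-equivalent examination as predictor, and the purpose is "to obtain an idea of the predictive ability of these early measurements compared with the measurements at term as used currently". The same item grades impairment as mild, moderate or severe at more than 1, 2 or 3 SD below the term-control mean on the Bayley-III Cognitive Composite. No cut-off is set for the early examination, and the article does not mention an AUC, sensitivity, specificity or predictive values.

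Under Sample size, 150 infants are said to allow correlations as small as 0.2 to be identified for Aims 2 and 3 with 80% power.

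**The concern.** The article chooses its performance measure and applies it to both kinds of model. For the linear models the choice is sound. For the logistic models there are three difficulties.

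- The description "representing the proportion of variability in the outcome explained by the model" belongs to a linear model. Logistic regression has several pseudo-R² versions, and the text does not say which is meant.
- The value of such an R² depends on how common impairment is, as well as on how well the examination works.
- Neither the R² nor the coefficient says how well the score separates infants who become impaired from those who do not, although the Background names discriminative and predictive validity before term as the evidence gap.

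What is at stake is how the Aim 3 result can be read. An early examination with a clear coefficient, and an R² near that of the term examination, could be reported as having predictive validity while most impaired infants would score on the wrong side of any reasonable cut-off. The reported figures would not show this.

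**Working it through.** **1. The plan's own figures.** Inputs from Sample size: n = 150, r = 0.2, 80% power, 5% significance.

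- Precision: 1.96/√150 = 0.160 SD, which reproduces the stated ±0.16.
- Correlation, by Fisher's z: power = Φ(atanh(0.2)·√147 − z). With one-sided 5% this is 79%. With two-sided 5% it is 69%, and the smallest r detectable with 80% power is 0.227. The article does not state sidedness for this test. That is a separate matter; here r = 0.2 serves only as the study's own benchmark, and it corresponds to a linear R² of 0.04.

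**2. What r = 0.2 means for a binary outcome.** The documents give no impairment rate and no examination cut-off, so both are assumed. Let score X and outcome Y be bivariate normal with correlation r, and call an infant impaired if Y ≤ c, where c = Φ⁻¹(p) and p is the proportion impaired. Then:

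- risk at score x: π(x) = Φ((c − r·x)/√(1 − r²))
- score density in impaired infants: f_I(x) = φ(x)·π(x)/p; in unimpaired infants: f_U(x) = φ(x)·(1 − π(x))/(1 − p)
- AUC = ∫ f_U(x)·F_I(x) dx
- sensitivity at 80% specificity = F_I(k), where F_U(k) = 0.20
- PPV = p·sens / (p·sens + (1 − p)·0.20)

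By numerical integration at r = 0.2:

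| Assumed impaired | AUC | Sensitivity at 80% specificity | PPV |
|---|---|---|---|
| 5% | 0.62 | 34% | 8% |
| 10% | 0.61 | 33% | 15% |
| 20% | 0.60 | 31% | 28% |
| 30% | 0.59 | 30% | 39% |

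Example for 20% impaired: PPV = 0.20×0.311/(0.20×0.311 + 0.80×0.20) = 0.062/0.222 = 28%. Simulation with 400,000 pairs gives the same picture (AUC 0.59–0.62, sensitivity 30–35%). So 65–70% of impaired infants are missed. At r = 0.4 the AUC is 0.69–0.74 and sensitivity 44–52%.

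**3. One R², many classification results.** With r fixed at 0.2, let the impaired proportion and the proportion flagged (lowest scores) each vary over 10–30%. Sensitivity then runs from 14% to 43%. With 20% impaired and 20% flagged it is 28%, so about 21–22 of 30 impaired infants among 150 are missed. At r = 0.5 (R² = 0.25) with the same rates it is 44%, so about 17 of 30 are missed.

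**4. Dependence on the R² version.** At r = 0.4, moving from 30% to 5% impaired raises the AUC from 0.69 to 0.74. Over the same change:

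- Tjur's R² falls from 0.095 to 0.046
- Nagelkerke's falls from 0.131 to 0.111
- McFadden's rises from 0.079 to 0.093

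The unnamed version therefore affects both the size of the figure and its direction of change with prevalence.

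**5. The planned early-versus-term comparison.** Here the outcome is fixed. At 20% impaired:

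| r | Tjur R² | AUC |
|---|---|---|
| 0.2 | 0.020 | 0.60 |
| 0.3 | 0.046 | 0.65 |
| 0.4 | 0.084 | 0.70 |
| 0.5 | 0.136 | 0.75 |

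Both measures put the examinations in the same order.

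**6. Precision of the added measures.** Wilson 95% intervals, with n the number impaired among 150: [p̂ + z²/2n ± z·√(p̂(1−p̂)/n + z²/4n²)]/(1 + z²/n). An observed sensitivity of 80% gives:

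- 15 impaired (10%): 55–93%
- 30 impaired (20%): 63–90%
- 45 impaired (30%): 66–89%
- 60 impaired (40%): 68–88%

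With 8 impaired (5%), 6 of 8 gives 41–93%. Specificity of 80% has an interval of about 71–87% across these rates.

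**The case against.** The strongest objection is that this is a condensed article without its analysis plan. It does not say that coefficients and R² are the only outputs, its wording about predictive ability is tentative, and an AUC from a planned logistic model is the kind of detail an analysis plan may add. This stands against inferring that missed cases will never be estimated: the article shows only that no such measure is planned in it. It does not remove the point, because the article does fix a measure for the binary outcomes, and that measure suits them poorly.

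A reader might also infer that R² would misrank mild, moderate and severe impairment, or distort the early-versus-term comparison. The document does not support this. It ranks no impairment grades, and for a fixed outcome R² and AUC order the examinations alike (step 5). The reversal across prevalences also depends on the R² version (step 4).

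Third, the Background sentence is rationale about what health professionals need. The study does not promise a screening test or a rule for individual infants, and its sample size rests on correlations. That is fair, and it is why the defect lies in item 3 of the analysis section. Even so, main aim 3 is predictive validity, and the same Background names discriminative validity as lacking.

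Finally, a score chosen to give 80% specificity is derived from the data, so it is not a cut-off set in advance, and with few impaired infants the intervals are wide. Both are correct and limit how strongly the fix can be put.

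**Conclusion.** The point holds as a cheap improvement. For the binary impairment outcomes of Aim 3, the article relies on coefficients and an R² that is not uniquely defined for logistic models, varies with prevalence and does not show discrimination. At the study's benchmark of r = 0.2, the AUC would be about 0.59–0.62, and about two thirds of impaired infants would be missed at 80% specificity.

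These sizes assume bivariate normality and 5–30% impaired, neither of which the documents give. That the R² is the wrong kind of measure for a binary outcome does not depend on those assumptions. The models themselves stand, as do the analyses of continuous outcomes and the ordering of early against term examinations.

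**What to change.** In Data collection & analysis, item 3, for the binary impairment outcomes:

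- Report the AUC with 95% CI for each early examination and for the term examination as the main performance measure. Compare them in the same infants where possible, since serial assessments stop at term or discharge and time points may include different infants.
- If an R² is kept, name its version.
- Add sensitivity, specificity and predictive values with CIs as a descriptive supplement. Use a published cut-off where one exists; otherwise use a fixed specificity and label the cut-off as data-derived.

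Keep coefficients and R² for the continuous outcomes.

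The cost is a change of wording and a few more outputs from models already planned, with no new data. The downside is wide intervals where few infants are impaired (step 6), which should be shown.

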
### Project overview

This observational study will document the evolution of neurobehavioural development in very preterm infants (defined as <30 weeks gestation) and parental psychological wellbeing during the first two years of their child’s life using serial measurements from birth. The influence of perinatal variables and parental wellbeing on the neurobehavioural pathway will be examined, along with the relationship between early neurobehaviour trajectories and MRI findings at term equivalent age and developmental outcomes at one and two years’ CA. The relationships between parental psychological wellbeing, parent–child interaction and child developmental outcomes will also be described. A control group of infants born at term will also be recruited in the neonatal period to allow comparison in outcomes and to provide a local reference group.

